## Aim

The aim of this study was to determine the variation in appendicectomy surgery wait times between rural and urban areas in Western Australia after initial presentation and diagnosis at an emergency department. Within these populations, selected outcome measures will be examined by time from:Initial presentation for the presenting complaint at an emergency department to the patient being seen by a general surgery registrar or consultant.Time from patient being seen by a general surgery registrar or consultant to surgery being performed.

The reason for taking data based on the two separate time frames is that by recording time between initial emergency department presentation to the patient being seen by the general surgery registrar or consultant, it will be possible to account for those patients who are not immediately diagnosed and then go on to have a delayed diagnostic laparoscopy and appendicectomy and evaluate and measure the magnitude of outcome impacts that an increased duration of this time could produce. Furthermore, the case report forms collect data on previous presentations of the same presenting complaint within the past week to capture any *prior premature discharge from the same site on initial evaluation of presenting complaint*.

This will allow examination of the effect of both triage wait times and timing of surgery after diagnosis on perforation, operation duration, and length of stay amongst each of the subpopulations.

Additionally, it is hoped to establish the rate of negative appendicectomies in urban and rural areas in Western Australia and if necessary make suggestions preoperatively to reduce their incidence.

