### Sample size

There are over 1600 participants that are planned to be included. This estimate was obtained from the Australian Government Medical Statistics Record, which displayed 818 WA claims for MBS item number 30720, the code for the surgical operation to be examined within this study from July 2022 to June 2023. Assuming this is representative for the beginning of 2022 to the end of 2023, the study window for this project, the number of participants can reasonably be estimated to be double this figure.

Amongst the metropolitan hospitals (Royal Perth Hospital, Sir Charles Gairdner Hospital, Fiona Stanley Hospital and Armadale Health Service), there will be 350 participants each, and at the rural hospitals (Albany Hospital, Bunbury Hospital, Broome Health Campus, Geraldton Hospital and Hedland Health Campus), there will be 50 participants each. This is reflective of the respective sizes of the hospitals.

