### Data analysis

Normally distributed data will be reported as mean (standard deviation (SD)), and non-normally distributed data will be reported as median (interquartile range (IQR)). Independent *t*-tests or ANOVAs will be used for normally distributed variables, Mann–Whitney *U* and Kruskal–Wallis tests will be used for non-normally distributed continuous or ordinal variables, and chi-squared tests will be used for categorical variable comparisons. When comparing appendicectomy wait times with complication incidence during the data analysis phase, a *P* value of 0.05 will be used to determine statistical significance. There will be no interim analysis or audit planned due to the grouping of data sets over four data collection periods. As this is a retrospective observational cohort study, there are no plans to deviate from the original protocol statistical plan or study design.

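### The effect of waiting is to be examined within rural and urban patients, but no stated test compares the two effects; with 1400 v 250 patients, separate tests invite an unsupported contrast

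*Protocol article*

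**What the plan says.** The protocol article's Aim section sets up the analysis by population: "Within these populations, selected outcome measures will be examined by time from" two intervals, first from emergency presentation to surgical review, then from review to operation. It says this will show the effect of both intervals "on perforation, operation duration, and length of stay amongst each of the subpopulations".

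The Data analysis section lists t-tests or ANOVAs for normally distributed variables, Mann–Whitney and Kruskal–Wallis tests for other continuous or ordinal variables, and chi-squared tests for categorical ones. Its only threshold is introduced by "When comparing appendicectomy wait times with complication incidence during the data analysis phase", where a P "value of 0.05 will be used to determine statistical significance". The section also says that no departure from the statistical plan is foreseen.

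The Sample size section fixes the group sizes. At each of four metropolitan hospitals "there will be 350 participants each, and at the rural hospitals", of which five are listed, "there will be 50 participants each".

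**The concern.** The article plans an effect estimate or test in each of two groups of very unequal size and names nothing that compares the two effects. A study built around a rural–urban contrast is likely to be read for whether delay has different consequences in the two settings. If all that is available is one P value per group, a significant urban result beside a non-significant rural one is easily taken as a difference. It may reflect only the larger rural standard error. The practical risk is false reassurance about delay in rural hospitals. The Introduction already offers several reasons why rural care may differ, so a spurious contrast would find a ready explanation.

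**Working it through.** **Group sizes (Sample size section).** Urban: 4 × 350 = 1400. Rural: 5 × 50 = 250. Sum: 1650. The stated total ("There are over 1600 participants that are planned to be included") comes from a source that "displayed 818 WA claims for MBS item number 30720" in one year, doubled: 2 × 818 = 1636. The two totals differ by 14, so the plan's figure is reproduced. Ratio: 1400 / 250 = 5.6. With the same outcome variance and the same spread of waits in both groups, the rural standard error is √5.6 = 2.37 times the urban one.

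**Assumptions.** The article gives no effect size, event rate, split of waits or power. I assume two-sided 0.05, the same true effect in both groups, and independent patients.

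**Formulae.**
- Urban expected z = 1.96 + z(urban power).
- Rural expected z = urban z × √(250/1400) = urban z × 0.423.
- Rural power = P(|Z + rural z| > 1.96).
- Urban only = urban power × (1 − rural power).
- Rural only = rural power × (1 − urban power).

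At urban power 90%: urban z = 1.96 + 1.28 = 3.24; rural z = 3.24 × 0.423 = 1.37; rural power = 0.278; urban only = 0.90 × 0.722 = 0.650; rural only = 0.10 × 0.278 = 0.028.

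| Urban power | Rural power | Urban only | Rural only |
|---|---|---|---|
| 50% | 13% | 43% | 7% |
| 80% | 22% | 62% | 4% |
| 90% | 28% | 65% | 3% |
| 95% | 33% | 64% | 2% |
| 99% | 44% | 55% | 0.4% |

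**Check with assumed event rates.** Short and long waits are split 50/50, with the outcome in 20% of patients after a short wait:

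| Rate after long wait | Urban power | Rural power | Urban only | Rural only |
|---|---|---|---|---|
| 20% (no effect) | 5% | 5% | 5% | 5% |
| 25% | 61% | 16% | 52% | 6% |
| 28% | 94% | 32% | 64% | 2% |
| 30% | 99% | 45% | 55% | 0.4% |
| 35% | 100% | 76% | 24% | 0% |

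A 30/70 split changes little (20% v 28%: 64% urban only, 3% rural only). With equal groups of 825 and 20% v 28%, each one-sided result occurs in 18% of studies, so the direction comes from the unequal split.

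**Direct test of the difference.** In 20,000 simulated studies per scenario with the same true effect in both groups (20% v 20% to 30%), a test of urban effect minus rural effect rejected in 5.1% to 5.7%, close to nominal. Its power is low. For a standardised effect of 0.2 in urban and 0 in rural patients with a 50/50 split, SE = √(4/1400 + 4/250) = 0.137, 0.2/0.137 = 1.46, and power = Φ(1.46 − 1.96) ≈ 31%. For 0.3 and 0.4 it is 59% and 83%.

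**The case against.** A reader might infer that the plan tests waiting in each group at 0.05 and will conclude that delay matters in urban but not rural hospitals. The article does not say this. The 0.05 sentence concerns complications and names no subpopulations. The sentence about subpopulations lists three other outcomes and names no threshold. Applying the threshold within each group joins the two sections. The rural–urban contrasts that are announced, such as wait times and negative appendicectomy rates, are direct comparisons that the listed tests can make.

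A reader might also infer that the imbalance alone produces the contrast, and always in one direction. The working does not support that. A real effect of small to moderate size is needed, the reverse result also occurs, and at urban power 20% or 30% the urban-only result falls to 19% or 27%. No effect is a live possibility, because the Introduction cites evidence that short delays do not increase complex appendicitis.

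Further, the Aim section also intends to measure the size of the impact, ANOVAs are not restricted to one factor, and a fuller analysis plan may specify an interaction. These points limit the wording and the severity. They do not remove the point: the article states the stratified examination, the group sizes and a list of tests from which it foresees no departure. For binary outcomes such as perforation it names only chi-squared tests.

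**Conclusion.** The point holds as a limited one. As stated, the plan examines the effect of waiting within each population and gives no means of comparing the rural effect with the urban one. Under a shared real effect of small to moderate size, separate tests would be significant in urban patients only in roughly 43% to 65% of studies over the urban powers tabulated, and in rural patients only in about 0.4% to 7%. A direct test would wrongly claim a difference about 5% of the time. These figures rest on the planned 1400 and 250 patients, two-sided 0.05, equal true effects and independent patients. Clustering within the nine hospitals is ignored and would lower power in both groups. The urban-but-not-rural conclusion is a foreseeable misreading that the plan invites. The change is a cheap improvement, not the repair of a stated false inference.

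**What to change.** In the Data analysis section, estimate the effect of each wait interval in one model on all patients, with rurality and a wait-by-rurality term. Report the rural and urban effects side by side with 95% CIs, without labelling each as significant or not. State that the effects will be called different only on the interaction estimate and its CI, and that a non-significant interaction will not be read as equal effects.

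The cost is one model term and a few sentences; no new data are needed. The downside is an imprecise interaction estimate at these group sizes, which is why the two group estimates with their CIs must stand beside it.

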## Audit standards for outcome measures

The optimal timing of appendicectomy for uncomplicated acute appendicitis should be within 12 h of initial presentation at an emergency department [1].

Laparoscopic appendicectomy approach should be performed unless contraindicated [3].

### Primary outcome measure

Wait time from presentation (hours) to diagnosis and then surgery. This is the number of hours from initial presentation at an emergency department until review by the surgical team, diagnosis, and then surgery. These parameters will be recorded on the case report forms as date and time and will be used to compare such wait times between rural and metropolitan hospitals.

### Secondary outcome measures

#### Rate of laparoscopic appendicectomy

This is the number of appendicectomies performed in rural and metropolitan hospitals. This will allow us to explore the overall rate compared to rates of negative appendicectomies in the specified hospitals.

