Following data collection, only case report forms with > 95% data completeness will be accepted for pooled analysis. Centers with > 5% missing data points will be excluded and collaborators from those centers withdrawn from the published list of citable collaborators. This is in order to provide some leeway for potential missing data, while also acknowledging that case report forms with ≥ 5% missing data may not be useful for our purposes. As the data originates from emergency department records, there is no perceived risk of including false or unused data. This study RGS6483 has received HREC approval by the Royal Perth Hospital HREC Ethics Committee, with a waiver of consent obtained and the HREC was notified of amendments to the protocol made on April 21, 2024.

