### Criteria

Inclusion criteria:(i)All patients who undergo an appendicectomy during the study period.(ii)Age 16 years or older at time of presentation

Exclusion criteria:(i)Previous appendicectomy or right hemi-colectomy or total colectomy.(ii)Current pregnancy at time of presentation

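### The secondary outcome named as a laparoscopic rate is defined as a count of all appendicectomies, so as written it measures hospital volume and not surgical approach

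*Protocol article*

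**What the plan says.** The Audit standards section of the protocol article sets two standards. One concerns surgery within 12 hours of presentation. The other concerns approach: "Laparoscopic appendicectomy approach should be performed unless contraindicated".

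Under Secondary outcome measures, one outcome carries the heading "Rate of laparoscopic appendicectomy". Its text has two sentences. The first is the definition: "This is the number of appendicectomies performed in rural and metropolitan hospitals". The second gives the purpose: "This will allow us to explore the overall rate compared to rates of negative appendicectomies in the specified hospitals". Neither sentence mentions laparoscopy, and no other section defines a laparoscopic proportion.

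Three other places bear on how the outcome would behave:

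- Criteria, first inclusion criterion: "All patients who undergo an appendicectomy during the study period" (aged 16 or over, subject to the exclusions).
- Sample size: 350 participants at each of four metropolitan hospitals and 50 at each of five rural ones, with the remark "This is reflective of the respective sizes of the hospitals".
- Data analysis: "chi-squared tests will be used for categorical variable comparisons".

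**The concern.** The heading promises a rate and an approach. The definition supplies neither. A single dropped word is an unlikely explanation, because the sentence on purpose also speaks of the overall figure and sets it beside the negative appendicectomy rate.

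This is the only listed outcome that names laparoscopy. If it is followed literally, the study reports hospital volume under a laparoscopic label, and the standard on approach goes unmeasured. A rural–urban contrast of the count would show that metropolitan hospitals are larger, which the Sample size section already says. If the team instead reports a true laparoscopic share, it departs from its published definition, although the Data analysis section says no departure from the statistical plan is intended. Nine sites with separate data-collection teams would also be working from a heading and a definition that point in different directions.

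**Working it through.** **Inputs, all from the protocol article.** Sample size: 818 claims in Western Australia in one year, doubled for the study window; 350 participants at each of 4 metropolitan hospitals; 50 at each of 5 rural hospitals; a planned total of over 1600. Criteria: the cohort consists of patients who had an appendicectomy. Methods: "Centers with > 5% missing data points will be excluded". The article gives no laparoscopic proportions, so those used in step 4 are assumptions.

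**1. The plan's own figure.** 2 × 818 = 1636, and 4 × 350 + 5 × 50 = 1400 + 250 = 1650. Both agree with the stated total. No stated number is wrong; the problem lies in the definition.

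**2. The outcome as written.** Let n be the number of eligible appendicectomies in a group and s the share done laparoscopically. The definition returns n.

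- Metropolitan: n = 1400. Rural: n = 250. Ratio 1400 / 250 = 5.6.
- Per hospital: 350 / 50 = 7.

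The share s does not enter, so the result is the same at s = 0 and s = 1.

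**3. Reading it as a rate over the cohort.** The only denominator available is the cohort, and every member of it had an appendicectomy. The rate is n / n = 100% in both groups, again whatever the value of s.

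**4. The outcome as a laparoscopic share.** The measure is (s × n) / n = s. With assumed shares for illustration:

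| Assumed share, metropolitan / rural | As written | As a share | Difference |
|---|---|---|---|
| 100% / 100% | 1400 vs 250 | 1400/1400 vs 250/250 | 0 points |
| 95% / 90% | 1400 vs 250 | 1330/1400 vs 225/250 | 5 points |
| 95% / 80% | 1400 vs 250 | 1330/1400 vs 200/250 | 15 points |

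The as-written column never moves. The share tracks practice.

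**5. Sensitivity to centre exclusion.** If the count is taken on accepted data, losing one metropolitan centre under the completeness rule gives 1400 − 350 = 1050, a fall of 350 / 1400 = 25%. Losing one rural centre gives 250 − 50 = 200, a fall of 50 / 250 = 20%. Surgical practice has not changed in either case. A share would move only to the extent that the excluded centre's practice differs from that of the others.

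**6. Fit with the named test.** A chi-squared comparison of approach needs each patient classed as laparoscopic or not. The definition creates no such class; a share does.

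**The case against.** The strongest case against is one of weight. This is one definition under one secondary outcome. The aims in the Abstract, Introduction and Aim sections concern wait times, their effect on outcomes, and negative appendicectomies; none of them mentions approach. The article condenses a fuller protocol, and the case report form, which covers management, may record approach. An analyst with the heading and the audit standard in hand could then work out the share that was meant. The rules for conversions and contraindications are details a condensed article may leave to other documents.

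Much of this is fair. The practical harm is small if the form records approach, and the absence of conversion and contraindication rules is not itself counted here as a fault. The figures 1400 and 250 are planned numbers, not an expected error, and nothing in the protocol says the raw counts will be tested against each other. The centre-exclusion figures illustrate how any raw count behaves. The chi-squared point follows from the definition and is not a second defect.

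It can also be argued that the heading is the stray element: both sentences describe overall volume as context for negative appendicectomies, so renaming would be the smallest repair. That reading is possible, but it leaves the laparoscopic standard with no matching outcome.

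None of this removes the contradiction. The article did not leave the definition to another document. It states one, and that definition disagrees with its own heading and with the audit standard.

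**Conclusion.** The point holds. As defined, the outcome returns cohort size (1400 against 250 on the planned numbers) or 100% in both groups if divided by the cohort, and carries no information on surgical approach. One of the two audit standards is therefore not measured by any outcome as written.

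The conclusion rests on the current wording and on the inclusion criterion; it needs no assumption about the true laparoscopic share. It does not extend to the primary wait-time comparison or the negative appendicectomy rate, and it does not claim that approach goes unrecorded. The definition should be corrected, but the error does not threaten the study's main aims.

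**What to change.** Redefine the outcome as the number of appendicectomies begun laparoscopically divided by all eligible appendicectomies, reported by hospital and by rural or urban group, and compared with the chi-squared test already named. Counting converted operations as laparoscopic, and reporting them separately, is a sensible convention; whichever rule is chosen should be written down.

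Check first that the case report form captures approach and conversion. Use contraindications to laparoscopy where they are recorded. Where they are not, report a crude laparoscopic share and do not call it compliance with the audit standard.

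If the total number of appendicectomies is also wanted, list it as a separate item under its own name, as the denominator for the negative appendicectomy rate. This also serves the volume reading of the present text.

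The cost is a wording change to one outcome if the form already holds these fields. If it does not, the fields must be added as well.

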#### Rate *of complex* appendicitis

This is the rate of appendicitis deemed complex based on various parameters. There are many grading systems such as the Sunshine Appendicitis Grading System (SAGS) as well as classification into simple (non-perforated) and complex (gangrenous or perforated) by Bhangu et al. [11]. Due to the retrospective nature of this study, it is impossible to determine whether all cases underwent intra-operative classification of severity using the such scoring. To address this, the case report forms in this study have been adapted to contain a macroscopic (physical) and microscopic (histological) evaluation of the case, which is more likely to have taken place and provides the same information.

##### Hospital stay length

This is the number of days that patients will be remaining in hospital from the date of their initial presentation in the emergency department. This will provide us with further information on the complexity of the cases as well as the post operative health needs of the patients undergoing appendicectomies.

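### Hospital stay is counted from emergency department presentation, so it contains the wait whose effect on stay is to be examined, and a positive bias is built in

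*Protocol article*

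**What the plan says.** Four statements in the protocol article bear on this point.

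- **Hospital stay length** (secondary outcome): "This is the number of days that patients will be remaining in hospital from the date of their initial presentation in the emergency department". The section gives two uses for the measure: the complexity of cases, and the "post operative health needs of the patients undergoing appendicectomies".
- **Primary outcome measure** (wait time): "This is the number of hours from initial presentation at an emergency department until review by the surgical team, diagnosis, and then surgery".
- **Aim**: wait is split into two intervals, presentation to review by a general surgery registrar or consultant, and that review to surgery. The data are to allow "examination of the effect of both triage wait times and timing of surgery after diagnosis on perforation, operation duration, and length of stay", within each subpopulation.
- **Data analysis**: t-tests or ANOVA for normally distributed variables, chi-squared tests for categorical ones, and for the rest Mann–Whitney and Kruskal–Wallis "tests will be used for non-normally distributed continuous or ordinal variables". No adjusted analysis is named. The threshold is stated for wait time against complications: a P "value of 0.05 will be used to determine statistical significance".

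No postoperative stay is defined anywhere in the article.

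**The concern.** Wait and stay share a start point, and both wait intervals in the Aim lie wholly inside the stay. Comparing stay across levels of wait therefore compares a sum with one of its own parts. Patients who wait longer will tend to have a longer total stay even if every patient recovers at the same pace after surgery.

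Length of stay is one of three outcomes that the Aim names for the effect of waiting. A positive result could be read as evidence that delay harms recovery when it reflects only the way stay was counted.

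Two further consequences follow. The Introduction suspects shorter surgical waits in rural hospitals; if so, part of any shorter rural stay would be the wait difference counted a second time. And a measure that includes preoperative time does not isolate postoperative need, which is one of its two stated uses.

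**Working it through.** **Planned size.** The Sample size section says "There are over 1600 participants that are planned to be included", from a source "which displayed 818 WA claims for MBS item number 30720" in one year. Doubling gives 2 × 818 = 1636. The per-site figures give 4 × 350 + 5 × 50 = 1400 + 250 = 1650. Both are over 1600 and agree within 1%. I use N = 1650 for the pooled analysis and n = 250 for all rural sites together.

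**Structure.** Let W be presentation to surgery, P surgery to discharge, and L the stay as defined. Then

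L = W + P, and Cov(W, L) = Var(W) + Cov(W, P).

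If wait has no relation to postoperative stay, Cov(W, P) = 0 and

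corr(W, L) = SD_W / √(SD_W² + SD_P²) > 0.

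**Assumptions.** The article gives no SDs. I take SD_W of 6, 12 and 24 h and SD_P of 24, 48 and 72 h, and assume that the 0.05 threshold applies to stay as well, two-sided. The chance of p<0.05 uses the Fisher z approximation, with z = atanh(r) × √(n − 3).

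Example, SD_W = 6 and SD_P = 72: r = 6/√(36 + 5184) = 0.083. At n = 1650, z = 3.38 and the chance is 92%. At n = 250, z = 1.31 and it is 26%.

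| SD_W (h) | SD_P (h) | Built-in r | p<0.05 at n = 250 | p<0.05 at n = 1650 |
|---|---|---|---|---|
| 6 | 24 | 0.243 | 97% | 100% |
| 6 | 48 | 0.124 | 50% | 99.9% |
| 6 | 72 | 0.083 | 26% | 92% |
| 12 | 24 | 0.447 | 100% | 100% |
| 12 | 48 | 0.243 | 97% | 100% |
| 12 | 72 | 0.164 | 74% | 100% |
| 24 | 24 | 0.707 | 100% | 100% |
| 24 | 48 | 0.447 | 100% | 100% |
| 24 | 72 | 0.316 | 99.9% | 100% |

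Every row has no true relation between waiting and postoperative stay, so the rate should be 5%.

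**Check with a planned test and whole days.** The table rests on a correlation, which the article does not plan, and ignores that stay is counted in days from a date. A simulation (500 runs per setting; gamma wait, independent lognormal postoperative stay, stay in calendar days) compared the longer-wait and shorter-wait halves by Mann–Whitney.

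| Wait mean/SD (h) | Postoperative mean/SD (h) | Rejection, n = 250 | Rejection, n = 1650 | Extra stay in longer-wait half (days) |
|---|---|---|---|---|
| 12/6 | 36/24 | 91% | 100% | 0.4 |
| 18/12 | 48/48 | 99% | 100% | 0.7–0.8 |
| 24/18 | 60/72 | 100% | 100% | 1.1 |

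Rounding to days does not remove the artefact. With stay counted from surgery in the same runs, Mann–Whitney rejection was 3.8 to 6.4% and Spearman rejection 4.0 to 6.2%, close to the nominal 5%.

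**Single intervals.** These figures are for total wait; the Aim uses two intervals. As an illustration, if they had equal variance and were uncorrelated, each would have SD_W/√2, and its built-in correlation would be 0.083/√2 = 0.06 to 0.707/√2 = 0.50. At the low end, r = 0.0587 gives z = 2.39 at n = 1650 (66%) and z = 0.92 at n = 250 (15%). The bias per interval is smaller but is still there.

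**Cancellation.** The association vanishes when Cov(W, P) = −Var(W), that is corr(W, P) = −SD_W/SD_P: from −6/72 = −0.08 to −24/24 = −1.0 over the assumed range.

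**Rural–urban comparison.** Mean L = mean W + mean P, so a difference in mean wait passes one for one into the difference in mean stay.

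**The case against.** The strongest reply is that total stay from presentation is a legitimate measure of resource use, that it is one secondary outcome, and that surgery date and time are recorded, so postoperative stay can be derived at analysis. All of that stands, and total stay may also bear on case complexity, the other stated use. But it does not answer the point: the article fixes the start of the clock, states that the effect of waiting on stay will be examined, and names only unadjusted tests.

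Some stronger readings are tempting and are not supported.

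- A reader might infer that a positive association is guaranteed. It is not. If sicker patients are operated on sooner and stay longer, Cov(W, P) is negative and can cancel or reverse the association. That would not rescue the analysis, because a real relation would then be masked. In small groups the bias may also miss significance.
- A reader might infer that the rural–urban comparison of stay merely repeats the primary outcome. Under the assumed SDs and independence, wait accounts for r² = 0.7% (0.083²) to 50% (0.707²) of the variance in stay. The comparison is contaminated by wait, not a duplicate of it.
- A reader might infer that days spent at home are counted for patients discharged and seen again within a week. The definition counts days remaining in hospital, and earlier presentations are recorded as a separate item. At most, initial presentation is ambiguous for these patients.

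**Conclusion.** The point holds as a built-in positive bias. It follows from the definitions of stay and wait together with the comparison announced in the Aim.

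Its size depends on SDs that the article does not give. Over the assumed ranges, a single favourable choice of SDs at the pooled N would show only the larger effects; the small-sample, wide-SD_P corner is much milder. At the pooled N, an analysis of total wait would nonetheless almost surely reach p<0.05 with no true relation to postoperative stay. Among rural patients alone, the result ranges from unlikely to near certain.

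The wait-time results for perforation and operation duration, the primary comparison of wait times and the negative appendicectomy rate are not affected.

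**What to change.** For all analyses of wait time against stay, and for any inference on postoperative need (including the rural–urban comparison), define the outcome as postoperative stay from surgery to discharge. Use days, or hours if discharge time is recorded; the article does not say that it is.

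Keep total stay from presentation as a descriptive resource-use measure, and state that it is not evidence of an effect of waiting.

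The cost is one line in the outcome definition. Surgery date and time are already recorded for the primary outcome, and any stay measure needs the discharge date, so a definition in days needs no new data item.
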